### Trial Design

This study is a 2-arm randomized controlled trial (RCT) that will test the efficacy of a web-based adaptation of iJobs. Participants will be randomly assigned (1:1 allocation) to either the intervention group, which benefits from the iJobs program, or a waiting list control group that will also receive the iJobs intervention 2 weeks after the intervention group finishes it. The 2 independent groups (intervention vs waiting list control group) will be crossed with 3 measurement times (ie, baseline, the postintervention time point, and 1-month follow-up). Hence, the design will be a 2 (intervention vs control) × 3 (baseline, the postintervention time point, and 1-month follow-up) factorial design.

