**Figure 2 figure2:**
[figure not shown]
Study design and procedure overview. t0: 2-3 weeks before iJobs; t1: randomization within 1 week before iJobs and pretest assessments for both groups; t2: posttest assessments within 1 week after iJobs for both groups; the control group starts now iJobs; t3: follow-up screening 1 month after iJobs for the intervention group; posttest assessments for the control group at the end of iJobs; t4: follow-up screening 1 month after iJobs for the waiting list group.

The participants from the intervention group will receive an email with the iJobs calendar and brief instructions. Afterward, they will receive an email with the platform login information. The username will be a random combination of digits (eg, IJ105) to ensure participants’ anonymity during the program. The account password is generated automatically by the platform. Once participants access their accounts, an introductive module containing the baseline measures questionnaire will be available on the platform. Meanwhile, the waiting list control group participants will receive an email with the iJobs period and a link to the baseline questionnaire.

On the iJobs’ platform, each module will be available for completion for 27 hours. After participants receive personalized written feedback on the platform from the team of counselors involved in the program, the following module will become automatically available for completion. After the last module, the posttest questionnaires will be available on the platform for 48 hours.

Further, 2 weeks after the intervention group finishes iJobs, the control group will start the intervention and go through the abovementioned steps. The questionnaire from the introductive module is the posttest measure for the control group.

Additionally, 1 month after the intervention, the participants who complete the posttest measures will be contacted to complete a brief questionnaire that evaluates their employment status and JSBs.

An overview of this study’s period is presented in Table 1.

**Table 1 table1:** Study timeline. Time points and outcome assessments for the intervention group and waiting list group from enrollment to follow-up.

			Time point^a^								
			Enrollment (t0)		Randomization and pretest measurement (t1)		Posttest measurement (t2)		Follow-up intervention group (t3)		Follow-up control group (t4)
Enrollment			✓								
Eligibility screen			✓								
Informed consent			✓								
Randomization					✓						

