**Assessments^b^**											
	Job-search intensity and effort			✓		✓		✓		✓	
	Job-search quality			✓		✓		✓		✓	
	Job-search self-efficacy			✓		✓		✓		✓	
	Self-esteem			✓		✓					
	Inoculation against setbacks			✓		✓					
	Psychological capital			✓		✓					
	Future career anxiety			✓		✓					
	Depression			✓		✓					
	Anxiety			✓		✓					
	Mental health complaints			✓		✓					
	Physical health	✓									
	Financial strain	✓									
	Sociodemographics	✓									
	Treatment adherence					✓		✓			
	Treatment satisfaction					✓		✓			
	System usability					✓		✓			
	Employment status	✓						✓		✓	
	Job quality (if applicable)							✓		✓	

^a^t0: 2-3 weeks before iJobs; t1: randomization within 1 week before iJobs and pretest assessments for both groups; t2: posttest assessments within 1 week after iJobs for both groups; the control group starts iJobs; t3: follow-up screening 1 month after iJobs for the intervention group; posttest assessments for the control group at the end of iJobs; t4: follow-up screening 1 month after iJobs for the waiting list group.

^b^For a detailed description, see the *Outcomes* section.

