### Outcomes

#### Primary Outcomes

##### Job-Search Intensity and Effort

We will use a contemporary version of Blau’s JSB scale, adapted to the Romanian context [16], to assess the frequency and intensity of participants’ job-search activities during the past 2 weeks. The scale consists of 16 items on a 5-point scale (1=never; 5=very frequent). Thus, 13 items measure job-search intensity (eg, “How often did you send your CV to potential employers?”), with a total score between 13 and 65, and 3 items measure job-search effort (eg, “You dedicated much of your time to job search.”), with a total score between 3 and 15. A higher score means a better outcome. JSBs will be measured at baseline, the postintervention time point, and follow-up.

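### The protocol contradicts itself on when controls take the posttest; under the Procedure it falls about 12 to 15 days after the intervention arm's, and on either reading it is tied to starting iJobs

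*Protocol article*

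**What the plan says.** Trial Design describes "a waiting list control group that will also receive the iJobs intervention 2 weeks after the intervention group finishes it". The Procedure repeats this: "2 weeks after the intervention group finishes iJobs, the control group will start the intervention and go through the abovementioned steps". It then fixes the control outcome: "The questionnaire from the introductive module is the posttest measure for the control group". For the intervention arm the Procedure says: "After the last module, the posttest questionnaires will be available on the platform for 48 hours".

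The Figure 2 legend gives a different timing: "t2: posttest assessments within 1 week after iJobs for both groups; the control group starts now iJobs". Footnote a of Table 1 agrees with the legend: "t2: posttest assessments within 1 week after iJobs for both groups". Both also list a posttest for controls at t3, at the end of their own iJobs, so the word covers two different control assessments.

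The module overview says that the introductive-module questionnaire has to be filled in before a participant is enrolled in the intervention. At baseline, controls receive their questionnaire by emailed link instead.

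Data Analysis uses one two-level time factor (baseline, postintervention) for both arms and takes the group-by-time interaction as the treatment effect. Job-search intensity and effort, a primary outcome, covers "job-search activities during the past 2 weeks". The anxiety and depression scales (GAD-7, PHQ-9) also look back two weeks.

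**The concern.** The interaction estimates the effect of iJobs only if the postintervention level of the time factor means the same thing in both arms. Under the Procedure it does not. The intervention arm is measured as its course ends, and controls about two weeks later, as theirs begins. Any change that comes with time alone, such as waning search effort, finding a job or natural change in mood, then enters the contrast alongside the treatment effect. Scales with a two-week recall would also describe largely different calendar periods in the two arms.

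A second problem does not depend on which timing is right. If the control posttest sits inside the introductive module, a control is observed only on entering the programme, whereas an intervention participant is observed after the last module. The circumstances that lead to an observed outcome therefore differ by arm.

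The contrast at stake is the main efficacy comparison for every primary and secondary scale.

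**Working it through.** No stated figure is to be reproduced here. The check is calendar arithmetic on the stated rules.

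**Inputs.** Day 0 is the start of iJobs in the intervention arm.
- iJobs lasts 2 weeks (Intervention), so the intervention arm finishes on day 14.
- Baseline falls within 1 week before iJobs (t1, Figure 2 legend): day −7 to 0.
- The intervention posttest is open for 48 hours (Procedure): day 14 to 16. Under the t2 definition it may run to day 21.
- Controls start 2 weeks after the intervention arm finishes (Trial Design, Procedure): 14 + 14 = day 28. Modules are open for 27 hours, about 1.1 days. Assuming this also holds for the introductive module, the control posttest falls on day 28 to about 29.
- Recall is 14 days for intensity and effort, GAD-7 and PHQ-9.

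**Formulas.**
- Elapsed time = posttest day − baseline day.
- Lag = control posttest day − intervention posttest day.
- Recall overlap = max(0, intervention posttest day − (control posttest day − 14)), when controls answer no earlier than the intervention arm.

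**Procedure reading.**
- Intervention elapsed: 14 − 0 = 14 to 16 − (−7) = 23 days.
- Control elapsed: 28 − 0 = 28 to 29.1 + 7 ≈ 36 days.
- Lag: 28 − 16 = 12 to 29.1 − 14 ≈ 15 days.
- Overlap: smallest max(0, 14 − 14) = 0, largest 16 − 14 = 2 days.

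**All readings.**

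| Reading | Elapsed, intervention (days) | Elapsed, control (days) | Lag (days) | Recall overlap (days) |
|---|---|---|---|---|
| Procedure, 48-hour window | 14–23 | 28–36 | 12–15 | 0–2 |
| Procedure, intervention posttest up to 1 week after iJobs | 14–28 | 28–36 | 7–15 | 0–7 |
| As first row, controls may open the module up to 1 week before their start (assumed, by analogy with t1) | 14–23 | 21–36 | 5–15 | 0–9 |
| As second row, same assumption | 14–28 | 21–36 | 0–15 | 0–14 |
| Figure 2 legend and Table 1 footnote | 14–28 | 14–28 | none systematic | 7–14 |

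In the first row the elapsed-time ranges of the two arms do not meet (23 is less than 28). Adding assessment day to the model would then rest on an assumed shape of the time trend, because no elapsed time is observed in both arms.

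**Observation of controls.** The legend and footnote change when t2 happens, but do not say that the control questionnaire is separate from the introductive module. The legend also has controls starting iJobs at t2. The tie between giving a posttest and entering the programme therefore remains on that reading too.

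**The case against.** The strongest reply is that the delay is not settled. The legend and footnote both define t2 as one time point for the two groups, and on that reading elapsed time is 14 to 28 days in each arm with no systematic lag. This stands, so the unequal timing is a conditional consequence and the contradiction is the firm finding.

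Several stronger inferences are tempting, but the document does not support them.
- A reader might conclude that the recall windows do not overlap at all. That holds only if the intervention arm answers on day 14 and controls on or after day 28; otherwise there is some overlap. Among the primary outcomes, a two-week recall is stated only for intensity and effort, not for job-search quality or self-efficacy.
- A reader might call arm and time fully confounded. That presupposes the Procedure with its 48-hour window; under the other readings elapsed times in the two arms meet or coincide.
- A reader might infer that controls who found work or lost interest are selectively lost. Nothing shows this. In Results, dropout from pretest to posttest is higher in the intervention arm (11/25, 44%) than in controls (10/38, 26%). What remains is that the route to being observed differs by arm, not that more controls are lost.
- A reader might put a standardised size on the bias. No outcome trend over time is given, so any figure would be an assumption.

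Two further points are fair. Anticipating treatment is part of any waiting-list design. And the intervention arm's recall covers its course weeks because a two-week recall follows a two-week course, whatever is done with controls.

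**Conclusion.** The concern holds in this form. The protocol gives incompatible rules for the control posttest, and the passages must be reconciled. If the Procedure is followed, the lag is about 12 to 15 days and the two-week recall windows share 0 to 2 of 14 days. If the intervention posttest may come up to a week after iJobs, the lag is 7 to 15 days and the overlap up to 7. The planned interaction, with its single two-level time factor, then combines the treatment effect with the extra elapsed time in controls. The direction and size of that bias cannot be derived from the document. If the legend and footnote are followed, there is no systematic lag.

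On either reading, taking the control outcome inside the introductive module ties its observation to starting treatment. The planned linear mixed model does not by itself remove selection that depends on unobserved outcomes.

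The figures assume a two-week programme run on schedule, controls answering at the start of their own iJobs, and a 27-hour opening for the introductive module. The table in the working shows how they widen when these are relaxed.

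**What to change.** Send controls the t2 questionnaire by emailed link, as is already done at baseline. Use the same opening and closing dates as the intervention arm's posttest, inside the t2 window already defined (within 1 week after the intervention arm's iJobs). Close it before controls get platform access, and keep it separate from the introductive module. This leaves the intervention arm's outcome as an immediate postintervention measure.

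Reconcile Trial Design, the Procedure, the Figure 2 legend and the Table 1 footnote to that window, and give the control assessment at t3 a different name. The passages also disagree on when controls start iJobs. The sponsor should settle that; the comparison needs only that the t2 window closes first.

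For the two sessions already run (130 randomized), report actual assessment dates by arm and examine how sensitive the results are to them, bearing in mind that adjustment is weak if elapsed times in the arms do not overlap.

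The cost is one additional email to controls. If the Procedure timing has been used so far, earlier and later sessions will also have different assessment schedules, which should be reported.

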Existing theories emphasize that unemployment is a cause of distress because unemployed people lose an essential social role (ie, status) and lack psychological basic needs fulfilled by one’s job (eg, time structure, social contact, activity, and financial security) [2]. Unsuccessful attempts to gain re-employment reduce the motivation of job seekers and affect their sense of competency and positive self-evaluations. In time, this can lead to mental health issues (ie, anxiety and depression). According to the results of a recent systematic review [11], JOBS improved participants’ self-esteem, self-efficacy (ie, job-search self-efficacy; JSSE), and ability to deal with setbacks (ie, inoculation against setbacks), which improved their well-being and mental health (on both the short and long term). Additionally, these coping mechanisms and job-search skills promoted and enhanced by JOBS are crucial for obtaining re-employment in a shorter period and obtaining a more qualitative job. Employment success and quality are predicted by job-search intensity and effort and job-search quality [12]. JOBS promotes job-search behaviors (JSBs; eg, beneficiaries make their job-search schedule) and the quality of those behaviors (eg, networking and practicing interviews).

The program’s effectiveness and popularity are based on its structure. It is a short-term intervention of 5 group sessions, encompassing almost all the components proven effective for job-search interventions [13]: *active learning, job-search skills, inoculation against setbacks, social support,* and *referent power.* During JOBS, participants learn the tasks they have to perform from the role of a job seeker and improve the necessary skills through group discussions, case studies, and role-playing exercises. They discover how to overcome potential setbacks in the re-employment process by brainstorming coping strategies, practicing their problem-solving skills, and receiving continuous social support from the trainers and beneficiaries.

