##### Job-Search Quality

We will use the Job Search Quality scale [17] to assess the quality of the job-search process, with precisely 4 components: goal establishment and planning, preparation and alignment, emotion regulation and persistence, and learning and improvement. The scale has 20 items on a 5-point scale (1=not at all applicable to me; 5=fully applicable to me). Goal establishment (ie, job-search goals and planning are clear, specific, and systematic) is measured with 7 items (eg, “I was determined to find a job.”); the total score ranges between 7 and 35. Preparation and alignment (ie, preparation of job-search activities in alignment with what the organizations are looking for in their applicants) is measured with 5 items (eg, “I carefully studied the website of organizations where I was going to apply.”); the total score ranges between 5 and 25. Emotion regulation (ie, self-control facilitating persistence in the job-seeking process; eg, “I persisted in my job search, even though it was unpleasant at times.”) and learning (ie, reflection on the job search and ways to improve it; eg, “I thought about other ways to find a job beyond those I had already tried.”) are measured with 4 items; the total score ranges between 4 and 20. A higher score means a better outcome. Job-search quality will be calculated at baseline, the postintervention time point, and follow-up.

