##### About JSSE

The JSSE [18] will be used to assess participants’ perception of their ability to gain employment. The scale has 20 items (eg, “I believe my job search will be successful”) on a 5-point scale (1=a little; 5=a great deal), with a total score between 20 and 100. A higher score means a better outcome. JSSE will be measured at baseline, the postintervention time point, and follow-up.

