##### Job Quality

The job quality will be measured at follow-up only for the participants who found employment, with 4 questions (a dichotomous question and 3 questions on a 10-point Likert scale; eg, “How much do you like your current job?”; 1=not at all and 10=very much). Specifically, we will assess the satisfaction with the professional domain, overall tasks, and salary.

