#### Data Analysis

We will use data from all the participants eligible for this study who completed the pretest measures. The data will be analyzed using the intent-to-treat framework with linear mixed model procedures. Intention-to-treat is based on the principle “once randomized, always analyzed.” It is a pragmatic approach to avoid bias in estimating the effect of treatment assignment in RCTs. We will use the linear mixed model approach without ad hoc imputations because it is more powerful than other options for studies with a high percentage of missing data [31].

For all the outcomes, time (baseline vs the postintervention time point) will be set as the within-group factor, and trial condition (intervention vs waiting list control group) will be used as the between-groups factor. We will analyze these 2 variables together with the entire set of outcomes (baseline vs postintervention comparison for the primary and secondary outcomes) to estimate the intervention’s effect size. Baseline to 1-month follow-up comparisons will be made to test how much the primary outcomes are preserved in time. We will also conduct separate analyses for each outcome with group, time, and group-by-time interaction as fixed effects and a random intercept for subjects with an identity covariance structure. The group-by-time interactions express the mean outcome change between the 2 trial groups from baseline to posttreatment.

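### The Procedure gives a narrower 1-month questionnaire than Table 1 and the Outcomes section, and sends it only to posttest completers, so some planned follow-up data would not be collected

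*Protocol article*

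**What the plan says.** **Procedure.** The 1-month contact is described as follows: "the participants who complete the posttest measures will be contacted to complete a brief questionnaire that evaluates their employment status and JSBs". This sentence sets both the content of the questionnaire and who receives it.

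**Outcomes.** Each of the three primary constructs has its own schedule:
- Intensity and effort: "JSBs will be measured at baseline, the postintervention time point, and follow-up".
- Job-search quality: "Job-search quality will be calculated at baseline, the postintervention time point, and follow-up".
- Self-efficacy: "JSSE will be measured at baseline, the postintervention time point, and follow-up".

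Under other measures, "The job quality will be measured at follow-up only for the participants who found employment".

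**Table 1.** All three primary constructs, employment status and job quality are ticked at t3 (intervention follow-up) and t4 (control follow-up).

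**Data Analysis.** The analysis uses all eligible participants with pretest data, in linear mixed models without imputation. It adds that "Intention-to-treat is based on the principle “once randomized, always analyzed". For the later time point, "Baseline to 1-month follow-up comparisons will be made to test how much the primary outcomes are preserved in time". This is not limited to one primary construct.

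**The concern.** There are two separate problems in one sentence.

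**Content.** The article states two different 1-month batteries. Whoever builds the form from the Procedure will leave out scales that Table 1, the Outcomes section and Data Analysis all rely on. Data not collected at 1 month cannot be recovered later, so the question of whether gains last would go unanswered for those outcomes.

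**Recipients.** Completing the posttest is an event after randomisation. Making contact depend on it means that people who stop early are not asked, rather than asked and silent. This matters most for re-employment. After enrolment it is assessed only at follow-up, and the mediation and moderation hypotheses (H6 and H7) both use it. A participant with no follow-up contact contributes nothing to it.

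The rule also selects on different things in the two arms. In the intervention arm the posttest opens on the platform after the last module, and each module opens only after feedback on the one before, so reaching it appears to require working through the programme. In the control arm, according to the Procedure, the posttest is the introductory-module questionnaire, answered before any iJobs content.

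**Working it through.** **1. What JSBs covers.** The Outcomes section uses the abbreviation for the intensity and effort scale ("JSBs will be measured at baseline, the postintervention time point, and follow-up", under that heading). The Background treats behaviours "and the quality of those behaviors" as two things. On this usage the Procedure sentence covers one primary construct of three. On a broader reading, helped by the Specific Objectives, which speak of quality as an attribute of JSBs, it covers two. JSSE is absent on either reading.

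**2. Content side by side at 1 month.**

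| Measure | Procedure | Outcomes | Table 1 (t3, t4) |
|---|---|---|---|
| Intensity and effort (16 items) | yes | yes | yes |
| Job-search quality (20 items) | no (yes if JSBs is read broadly) | yes | yes |
| JSSE (20 items) | no | yes | yes |
| Employment status | yes | yes | yes |
| Job quality, if employed | not named | yes | yes |

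Primary items needed at follow-up: 16 + 20 + 20 = 56. Items left out by the Procedure: 20 + 20 = 40 on the article's own usage, or 20 on the broad reading.

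**3. What is lost in the analysis.** Data Analysis tests every outcome from baseline to posttest through the group-by-time interaction. Those tests need no 1-month data, so H2 and H3 remain testable. Only the baseline-to-1-month comparison fails for the omitted scales.

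**4. Effect of the contact rule.** The inputs are in the Results section, which gives pretest-to-posttest dropout of 11/25 and 10/38, and 42 participants with complete data (14 and 28).

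The plan's figures reproduce:
- Intervention: 11/25 = 44.0%; 25 − 11 = 14 remain.
- Control: 10/38 = 26.3%; 38 − 10 = 28 remain.
- Total with posttest: 14 + 28 = 42.

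Follow-up pool:
- All pretest completers: 25 + 38 = 63.
- Pool under the Procedure: 42.
- Never contacted: 11 + 10 = 21, and 21/63 = 33%.
- Share still contacted: 14/25 = 56% of intervention, 28/38 = 74% of control.

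**5. Precision of the arm difference.** The odds ratio for missing the posttest is (11 × 28)/(14 × 10) = 2.2, with Fisher exact p = 0.18. The imbalance is not established by these data.

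**6. What non-contact means for re-employment.** Suppose all 14 contacted intervention participants reply and x are employed. The share among the 25 pretest completers then lies anywhere from x/25 to (x + 11)/25, a width of 11/25 = 44 percentage points. In the control arm the width is 10/38 = 26 points. The contact rule produces this range before any non-response is counted.

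**The case against.** **The Procedure sentence is only a summary.** The next sentence points to Table 1, whose footnote sends the reader to the Outcomes section, and all of these agree with Data Analysis. The omission may therefore never reach the actual form. That is fair, and it makes the loss conditional on staff following the Procedure. The article still describes two batteries, no sentence reconciles them, and JSSE cannot be read into the shorter one.

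**The intention-to-treat analysis is not contradicted.** A reader might infer from the once-randomised principle that the contact rule breaks it. The documents do not support that. The analysis set is everyone eligible with pretest data, and a linear mixed model keeps a person with only a baseline value, under a missing-at-random assumption. The objection stands as far as the analysis set goes. It is a reason to tolerate missing data that cannot be avoided, and does not justify failing to ask.

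**Full contact would not give a clean employment comparison.** The Limitations section already says the arms cannot be compared on employment at follow-up, because the waiting list also receives iJobs. This stands and limits the gain. The disclosure concerns exposure of the control arm, however, and not who is contacted. The baseline-to-1-month comparisons and any use of re-employment in H6 and H7 still depend on who replies.

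**Conclusion.** The point holds on both counts, with limits.

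- **Content.** The Procedure conflicts with Table 1, the Outcomes section and Data Analysis. If it is followed, the 1-month comparison is impossible for JSSE, and also for quality on the article's own use of JSBs.
- **Recipients.** The contact rule is an avoidable source of missing 1-month data: 21 of 63 pretest completers (33%) so far. This assumes that the interim dropout is representative and that the rule is applied as written.

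Three stronger readings are not supported:
- That H2 and H3 become untestable. Their baseline-to-posttest tests do not use follow-up data.
- That only 42 of 130 randomised (32%) can be contacted because of this rule. Of the 130, 130 − 63 = 67 have no pretest in the reported denominators. They were lost earlier and lie outside the stated analysis set.
- That differential dropout is shown. With 11/25 against 10/38 the difference is imprecise (p = 0.18). The case rests on how the rule is built.

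This is worth correcting, but it does not threaten the main posttest analysis.

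**What to change.** Reword the Procedure sentence to say that, 1 month after the intervention, all participants who completed the pretest and have not withdrawn are contacted, whether or not they completed the posttest. They complete the Table 1 battery: intensity and effort, job-search quality, JSSE, employment status and, if employed, job quality.

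This also removes a side ambiguity. For controls, the Procedure calls the introductory-module questionnaire the posttest, while the Figure 2 caption and the Table 1 footnote also place a control posttest at the end of iJobs. Once contact no longer depends on the posttest, it does not matter for follow-up which one is meant.

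If a short form is a deliberate choice, the alternative is to narrow Table 1, the Outcomes section and Data Analysis to match it. That settles the text but gives up the 1-month comparison for the dropped scales.

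**Cost.** One sentence, and more messages to people whom the Procedure already reaches by email. The form would be longer by up to 40 primary items plus the 4 job-quality questions for those employed, and the response from earlier dropouts will probably be low. The change therefore reduces the missing data but will not remove it.
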